### Additional data sources

Our data will be linked to nationwide Swedish health registers including the National Patient Register (NPR),^43^ the Prescribed Drug Register (PDR),^45^ the Medical Birth Register^44^ and the National Quality Register for Specialised Eating Disorder Treatment (Riksät/Stepwise).^46^ Register linkage is conducted by government agencies via the Swedish personal number. The NPR provides data on all inpatient care since 1987 and around 80% of specialised outpatient care since 2001,^43^ using International Classification of Diseases 10th revision classification since 1997. We will use the NPR to identify ARFID-related diagnoses; other EDs and psychiatric, neurodevelopmental and somatic conditions; as well as to track healthcare utilisation over time. Evidence shows strong agreement between ED diagnoses in the NPR and in Riksät/Stepwise, confirming the validity of NPR data for research.^53^ The PDR provides data on all drug prescriptions dispensed since 2005, with active drug ingredients categorised using the Anatomical Therapeutic Chemical (ATC) Classification System.^45^ We will use ATC codes to identify prescribed nutritional supplements and enteral nutrition relevant to ARFID and medication utilisation over time. Riksät/Stepwise contains data on ED treatment from around 100 specialised and general psychiatry units across 21 regions since 1999. We will extract diagnoses and clinical characteristics, such as symptom severity and impairment. Riksät offers broader coverage and includes DSM-IV subtypes, providing more extensive information than the NPR.^46^

For GWAS, we will combine our data with other completed, ongoing and planned collections conducted by PGC-ED. Refer to table 2 for the expected sample sizes at the time of analysis.

**Table 2 T2:** Sample sizes and availability of genotypes for the ARFID-GWAS meta-analysis

Study	Cases	Controls	Age	Available by
ASTRI	300	⁓18 000	6–12	Available
ARIES	1500	500	6–14	May 2025
ARFID-GEN	⁓3000	/	6–99	September 2024
EDGI2	⁓3000	⁓1300	15–99	March 2026
PGC-ED	1200	⁓42 000	15–99	Available

ARFID, avoidant/restrictive food intake disorder; ARFID-GEN, ARFID–Genes and Environment; ARIES, ARFID InitiativE Sweden; ASTRI, ARFID in the Swedish Twin Registry Initiative; EDGI2, Eating Disorders Genetics Initiative 2; GWAS, genome-wide association studies; PGC-ED, Eating Disorders Working Group of the Psychiatric Genomics Consortium.

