#### Statistical power

For the phenotypic analyses, we would need 394 participants in both case and control group to detect a small effect size (0.2) at an alpha level of 0.5 and 80% power and are, therefore, well powered.

For GWAS analyses, we set α=5×10^−8^. GWAS meta-analysis will include >71 000 samples (9000 cases; 62 360 controls; table 2) and will have >80% power to detect common variants (minor allele frequency [MAF]>5%) with modest effect sizes (OR>1.25), and low frequency variants (MAF>1%) with moderate effect sizes (OR>1.59). We anticipate detecting medium to large genetic effects for ARFID, considering a twin-based heritability estimate of 79%^5^ and are, therefore, adequately powered. No published studies exist on the gut microbiota in ARFID to guide our power analyses. However, our given sample size of 100 cases and 100 controls exceeds sample sizes of most published studies on the gut microbiota in AN. We expect to be adequately powered to detect medium to large effect sizes.

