##### Genetic analysis

We will use the Ricopili software pipeline (Rapid Imputation for Consortias Pipeline, developed by PGC) including modules for preimputation (QC), principal component analysis, imputation and meta-analysis to process hundreds of GWAS data sets rapidly and consistently.^54^

First, we will conduct an independent within-disorder GWAS of the ARIES sample alone and then combine the ARIES sample with additional ARFID samples from the PGC-ED to conduct a GWAS meta-analysis. Post-GWAS analyses will include, among others, the analysis of X chromosome (chrX) variants; secondary GWAS analyses separately on females and males to evaluate the similarity to the results of the primary GWAS; clumping GWAS to convert significant single nucleotide polymorphisms (SNPs) (p<5×10^−8^) into regions; conditional and joint analyses; functional genomic integration; linkage disequilibrium score regression (LDSC) to estimate SNP-based heritabilities^55 56^; the calculation of rare copy number variants (CNVs) and CNV burden; the calculation of polygenic risk scores (PRS) using the p-thresholding method and a summary statistics version of Bayesian multiple regression (SBayesR)^57^; an ARFID presentation analysis examining the association between ARFID PRS and PARDI-AR-Q subscale scores sensory-based food avoidance, lack of interest in food or eating and fear; gene-wise tests of association with ARFID using multimarker analysis of genomic annotation^58^; the investigation of partitioned heritability using stratified LDSC,^59^ and whether genes associated with ARFID are enriched in certain tissues, cell types and pathways.

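### The GWAS meta-analysis power above 80% is computed from pooled totals; under Table 2 it depends on a control allocation that the article does not state, and the stated totals do not match the table

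*Protocol article*

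**What the plan says.** The Statistical power section fixes the threshold ("For GWAS analyses, we set α=5×10^−8") and gives the sample: "GWAS meta-analysis will include >71 000 samples (9000 cases; 62 360 controls; table 2"). From these totals it claims power above 80% at two points: the meta-analysis "will have >80% power to detect common variants (minor allele frequency [MAF]>5%) with modest effect sizes (OR>1.25"), and likewise for "low frequency variants (MAF>1%) with moderate effect sizes (OR>1.59").

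Table 2, in Additional data sources, is titled "Sample sizes and availability of genotypes for the ARFID-GWAS meta-analysis". It lists cases/controls as ASTRI 300/about 18,000; ARIES 1500/500; ARFID-GEN about 3000/none listed; EDGI2 about 3000/about 1300; PGC-ED 1200/about 42,000.

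The Genetic analysis section plans a GWAS of ARIES alone and then to "combine the ARIES sample with additional ARFID samples from the PGC-ED to conduct a GWAS meta-analysis".

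The power section closes with an argument from heritability: "We anticipate detecting medium to large genetic effects for ARFID, considering a twin-based heritability estimate of 79"%, from which it concludes that power is adequate.

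**The concern.** A meta-analysis combines within-stratum comparisons of cases with controls. Its information is the sum over strata, not the information in the column totals. The two agree only when cases and controls are spread across strata in similar proportions. Table 2 is far from that: ARIES has three cases per control and EDGI2 about 2.3, while ASTRI has 60 controls per case and PGC-ED 35. A third of all cases sit in a study with no listed controls.

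The power figure supports the Aim 2 expectation of genome-wide significant loci. If it is too high for the analysis that is run, the detectable odds ratios are too low and readers will take the absence of a hit as stronger evidence than it is. Separately, a total that is attributed to Table 2 should be the total of Table 2.

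**Working it through.** **Totals.** Cases: 300 + 1500 + 3000 + 3000 + 1200 = 9000, as stated. Controls: 18,000 + 500 + 1300 + 42,000 = 61,800, against 62,360 stated (560 fewer, 0.9%). All: 9000 + 61,800 = 70,800, against more than 71,000 stated (9000 + 62,360 = 71,360).

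**Method.** Two-sided α = 5×10⁻⁸ (sidedness is not stated; two-sided assumed), so the critical value is 5.451. Let q be the control allele frequency, and p the case frequency implied by the OR: p/(1−p) = OR·q/(1−q). Stratum information on the log OR:

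I = 1 / [1/(2·cases·p(1−p)) + 1/(2·controls·q(1−q))]

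Power = Φ(ln OR·√ΣI − 5.451). Effective N per stratum = 4·cases·controls/(cases + controls).

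**The article's figure, as one sample of 9000/62,360.**
- q = 0.05, OR = 1.25: p = 0.0617, I = 886.5, z = 0.2231 × √886.5 = 6.644, power Φ(1.193) = 88%.
- q = 0.01, OR = 1.59: p = 0.0158, I = 228.3, z = 0.4637 × √228.3 = 7.006, power Φ(1.555) = 94%.

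The claim reproduces. With 61,800 controls, power moves by about 0.1 point.

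**Each study with its own Table 2 controls.** Effective N: ASTRI 1180 + ARIES 1500 + EDGI2 3628 + PGC-ED 4667 + ARFID-GEN 0 = 10,975, or 35% of the pooled 31,424.
- OR 1.25: ΣI = 34.1 + 37.3 + 91.1 + 134.3 = 296.8, z = 3.844, power Φ(−1.607) = 5%.
- OR 1.59: ΣI = 9.1 + 8.2 + 20.2 + 35.7 = 73.2, z = 3.967, power Φ(−1.484) = 7%.
- ORs with 80% power: about 1.42 (MAF 5%) and 2.0 (MAF 1%).

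**Other allocations.** The groupings are assumptions; the article gives none.

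| Strata | Effective N | MAF 5%, OR 1.25 | MAF 1%, OR 1.59 |
|---|---|---|---|
| Own controls only | 10,975 | 5% | 7% |
| ARFID-GEN shares EDGI2's controls, others separate | 11,621 | 6% | 8% |
| ARFID-GEN shares PGC-ED's controls, others separate | 21,581 | 50% | 59% |
| ARIES+ASTRI / EDGI2 / ARFID-GEN+PGC-ED | 25,462 | 69% | 79% |
| ASTRI / ARIES / ARFID-GEN+EDGI2+PGC-ED | 27,374 | 76% | 85% |
| ARIES+ASTRI / ARFID-GEN+EDGI2+PGC-ED | 31,255 | 88% | 94% |
| One pooled sample (Table 2) | 31,424 | 88% | 94% |

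A stratified score-type calculation gives the same picture: 6% and 8% for own controls only, 86% and 91% for the two-stratum grouping.

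**Heritability.** Assume 1.5% prevalence, inside the article's 1–2%. Under an additive logistic model converted to the liability scale, one variant with MAF 5% and OR 1.25 explains about 0.07% of liability variance. A heritability of 79% is then about 0.79/0.00074 ≈ 1070 such variants, or very many smaller ones. The aggregate figure does not fix the effect of any single variant.

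**The case against.** The strongest reply is that strict within-study controls are not what the article describes. It counts ARFID-GEN's 3000 cases in the 9000, so it must intend to borrow controls for them. It runs all data through one common pipeline for quality control, principal components, imputation and meta-analysis, and refers to separate predetermined analysis plans, where control allocation may well be set out. All of this stands: the 5% and 7% are the bottom of a range, not the power of the planned analysis.

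A reader might also infer that the claim holds only for a single pooled sample. It does not need that: the two-stratum meta-analysis loses about 0.5% of effective N against full pooling and keeps both figures above 80%. But that grouping joins every case-heavy cohort to a control-rich one, and the article nowhere states it. Among the allocations tabulated, only it and full pooling put both figures above 80%.

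A reader might further infer that a null GWAS is the likely result. That does not follow. The calculation is at the boundary MAF, while the claim covers MAF above 5%: at OR 1.25, even with own controls only, the same formula gives 42% at MAF 10%, 77% at 15% and 92% at 20%. Per-variant power is also not the chance of finding nothing: with some 1000 boundary variants at about 5% power each, around 50 hits would be expected.

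Finally, the mismatch in totals is trivial in size, and the large control counts are marked approximate. That is true, but the text gives an exact 62,360 and cites the table for it.

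**Conclusion.** The concern holds in a conditional form. The power claim is right for pooled totals, but it is stated as fact for a meta-analysis whose strata are not given, and Table 2 alone does not support it. Across the allocations examined, power runs from about 5% to 88% at MAF 5%, OR 1.25, and from about 7% to 94% at MAF 1%, OR 1.59. This is more than detail left to an analysis plan, because the article itself publishes the number and the conclusion of adequacy. The documents do not show that the planned analysis is underpowered; they show that the reader cannot tell.

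The control and grand totals do not match Table 2, by under 1% and with no practical effect on power. The step from 79% twin heritability to sizeable per-variant effects and adequate power is invalid under any allocation.

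The results assume a two-sided test, an additive allelic model, Table 2 counts at face value, the same allele frequencies and OR in every stratum, and no loss to quality control or ancestry matching.

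**What to change.** - Reconcile 62,360 and the figure above 71,000 with Table 2: either restate them as 61,800 and 70,800, or correct the table.
- State the strata of the meta-analysis and name the controls used for ARFID-GEN, ARIES and EDGI2.
- Recompute power and the detectable ORs from the summed per-stratum effective sample sizes under that allocation. If the present figure is kept, say that it assumes merged strata with shared controls.
- Remove the inference from twin heritability to per-variant effect size and to adequate power.

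The cost is one recomputed and reworded paragraph, with no new participants. Unless the planned strata are close to full merging, the stated power will become less favourable.

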#### Data analysis

Research data will be pseudonymised for data analyses. We will follow predetermined statistical analysis plans for phenotype, genotype and gut microbiome data. All analyses will include age and sex/gender as covariates and be corrected for multiple testing.

##### Phenotypic analyses

We will describe the ARFID sample to present demographics; ARFID symptoms, onset and course; other ED pathology; food intake; co-occurring psychiatric, neurodevelopmental and somatic conditions and traits; treatment utilisation; environmental exposures; impairment and quality of life; and parental stress and ED pathology. Depending on the distribution, we will compute mean/SD or median/IQR for continuous variables, and *N*/percent for categorical variables. To compare ARFID cases with controls on all outcomes, we will conduct generalised linear modelling.

##### Genetic analysis

We will use the Ricopili software pipeline (Rapid Imputation for Consortias Pipeline, developed by PGC) including modules for preimputation (QC), principal component analysis, imputation and meta-analysis to process hundreds of GWAS data sets rapidly and consistently.^54^

First, we will conduct an independent within-disorder GWAS of the ARIES sample alone and then combine the ARIES sample with additional ARFID samples from the PGC-ED to conduct a GWAS meta-analysis. Post-GWAS analyses will include, among others, the analysis of X chromosome (chrX) variants; secondary GWAS analyses separately on females and males to evaluate the similarity to the results of the primary GWAS; clumping GWAS to convert significant single nucleotide polymorphisms (SNPs) (p<5×10^−8^) into regions; conditional and joint analyses; functional genomic integration; linkage disequilibrium score regression (LDSC) to estimate SNP-based heritabilities^55 56^; the calculation of rare copy number variants (CNVs) and CNV burden; the calculation of polygenic risk scores (PRS) using the p-thresholding method and a summary statistics version of Bayesian multiple regression (SBayesR)^57^; an ARFID presentation analysis examining the association between ARFID PRS and PARDI-AR-Q subscale scores sensory-based food avoidance, lack of interest in food or eating and fear; gene-wise tests of association with ARFID using multimarker analysis of genomic annotation^58^; the investigation of partitioned heritability using stratified LDSC,^59^ and whether genes associated with ARFID are enriched in certain tissues, cell types and pathways.

We will compare disorder-specific GWAS for ARFID, AN, BN and BED and transdiagnostic behaviours (eg, restriction, binge eating). Analyses will include, among others, the calculation of common variant-based genetic correlations (SNP-r_g_s) for ARFID and selected traits to investigate common genetic variation using GWAS summary statistics; generalised summary data-based Mendelian randomisation to investigate causal relationships between ARFID and selected traits; multitrait-based conditional and joint analysis (GCTA-mtCOJO)^60^ to investigate whether SNP associations for EDs can be traced back to their relationship with correlated traits such as type 2 diabetes, body mass index and depression; the calculation of disorder-specific SNP associations by conducting a case vs case GWAS (eg, ARFID vs BED) and multipolygenic scores^61^ by using the largest available GWAS summary statistics of psychiatric and somatic conditions and traits to predict selected outcomes (ARFID, AN, BN, BED); and genomic structural equation modelling^62^ to investigate the genetic architecture of ARFID compared with other EDs.

Finally, we will analyse whether ARFID is genetically associated with various psychiatric, neurodevelopmental, somatic and other relevant phenotypes by making use of the same methods outlined above. Summary statistics of selected traits are provided by other PGC working groups and the UK Biobank.

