ARFID is present in 1%–2% of the general population^5 6^ and was formally recognised in 2013.^7^ ARFID is a feeding and eating disorder characterised by an extremely restricted dietary quantity or variety resulting in significant weight loss, nutritional deficiencies, reliance on nutritional supplements and/or psychosocial impairment.^7^ In contrast to other EDs, ARFID occurs in approximately equal proportions of males and females,^6 8^ has an earlier age of onset^9^ and the restrictive eating is not primarily motivated by weight and shape concerns.^7^ ARFID is often accompanied by severe and sometimes life-threatening somatic and psychosocial comorbidities, leading to high social and financial burden for patients and their families.^10^,^14^ Despite the significant impairment, our knowledge on ARFID aetiology is limited. In part due to this insufficient understanding, evidence-based treatments are only starting to be developed^15^ and no specific treatment guidelines exist.^16^ A longer duration of untreated EDs other than ARFID has been found to decrease the likelihood of recovery.^17^ It is, therefore, likely that the lack of treatment options significantly contributes to the chronicity of ARFID.

ARFID is conceptualised as a single disorder; however, the Diagnostic and Statistical Manual of Mental Disorders fifth edition (DSM-5) describes three non-mutually exclusive presentations: (1) sensory-based food avoidance; (2) low appetite or interest in food and (3) fear of aversive consequences of eating. These symptom clusters overlap in a subset of individuals with ARFID (15%–51%).^818^,^20^ Comorbidities vary somewhat depending on the dominant presentation(s)^11 19^; for instance, sensory-based food avoidance has been shown to be more strongly related to neurodevelopmental conditions, low appetite or interest in food to mood disorders,^21^ and fear of aversive consequences to obsessive-compulsive disorder (OCD) and anxiety disorders.^11^

ARFID-related phenotypes such as appetite, food fussiness and food neophobia have been shown to be moderately to highly heritable.^22^,^25^ Our previous research using Swedish twin data further supports our aim of conducting a GWAS for ARFID: with a twin-based heritability of 70%–85%,^5^ ARFID is among the most heritable of EDs^26^ and of psychiatric conditions in general.^27^,^30^

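### The sex-specific GWAS are compared with the primary GWAS that contains the same people, which biases the comparison towards similarity; females should be compared with males.

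*Protocol article*

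**What the plan says.** The protocol article, under Genetic analysis, lists among the post-GWAS work "secondary GWAS analyses separately on females and males to evaluate the similarity to the results of the primary GWAS". This gives both the analysis and its comparator: each sex is set against the primary GWAS.

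The primary GWAS appears to pool both sexes. Under Data analysis, sex enters only as an adjustment variable: "All analyses will include age and sex/gender as covariates and be corrected for multiple testing". No separate sample is named for the sex-specific runs. The sequence of samples is given as "First, we will conduct an independent within-disorder GWAS of the ARIES sample alone and then combine the ARIES sample with additional ARFID samples" from the consortium.

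The only statement on sex balance is in the Background, about the disorder in general: "ARFID occurs in approximately equal proportions of males and females". Table 2 gives cases and controls per study, without a split by sex. The genetic correlations described later in the section concern other phenotypes: "the calculation of common variant-based genetic correlations (SNP-r_g_s) for ARFID and selected traits".

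**The concern.** The natural use of sex-specific GWAS is to see whether pooling hides differences between the sexes. The comparator chosen here is poorly suited to that. The pooled effect at a SNP is approximately a weighted average of the female and male effects, so either sex is being correlated with a quantity that contains itself. Some agreement is guaranteed by that structure even when females and males share no genetic effects.

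The usual remedy for overlapping samples does not solve this. The LDSC intercept absorbs sampling error shared between two GWAS. The part-whole relation lies in the true effects and remains after that error is removed.

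At stake is how the sex-specific results are read. A correlation of 0.87 with the primary GWAS looks like good agreement. At equal weights it corresponds to a between-sex genetic correlation of only 0.5. The article gives no benchmark that would tell a reader this.

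**Working it through.** The article states no figure on this point, so there is none to reproduce. The check asks what the planned comparison would show for a given true female-male correlation.

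**Inputs**
- Comparator: each sex against the pooled primary GWAS (Genetic analysis; Data analysis for sex as a covariate).
- Female weight w in the primary GWAS: not given for the analysed sample. Assumed 0.5, with 60:40, 70:30 and 75:25 as a range.
- True female-male genetic correlation r: not given. Assumed range −0.5 to 0.75.
- Equal variance of true effects in the two sexes: assumed.

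**Formula.** Write the primary effect as P = wF + (1−w)M, with F and M the true female and male effects. Then

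corr(F, P) = (w + (1−w)r) / √(w² + (1−w)² + 2w(1−w)r),

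and corr(M, P) follows by exchanging w and 1−w. At w = 0.5 both reduce to √((1+r)/2).

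**Equal weights**

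| True r (female-male) | Each sex against primary |
|---|---|
| −0.5 | √0.25 = 0.50 |
| 0 | √0.5 = 0.71 |
| 0.25 | √0.625 = 0.79 |
| 0.5 | √0.75 = 0.87 |
| 0.75 | √0.875 = 0.94 |

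True values from 0 to 1 are thus squeezed into the range 0.71 to 1.

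**Unequal weights, true r = 0**

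| Split | Larger sex against primary | Smaller sex against primary |
|---|---|---|
| 60:40 | 0.83 | 0.56 |
| 70:30 | 0.92 | 0.39 |
| 75:25 | 0.75/√0.625 = 0.95 | 0.25/√0.625 = 0.32 |

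These are correlations of true effects. No sampling error enters them, so an overlap correction leaves them unchanged.

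**Simulation with sampling error.** The check used 200,000 independent SNPs, equal weights, and independent female and male effects (r = 0), with genetic variance 0.5, 1 or 2 times the sampling variance in one sex.
- Against the primary GWAS: correlation 0.706 to 0.709, sign agreement about 75%.
- Females against males: correlation −0.002 to 0.003, sign agreement about 50%.

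The direct comparison recovers the true value of 0; the planned one shows 0.71.

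**Single loci.** Take loci with an effect in females only, female z-score mean 5 to 8 and male mean 0, that reach 5×10⁻⁸ in an equally weighted primary GWAS (z > 5.45). The male estimate then has the same sign as the primary in 99% (mean 5) to 71% (mean 8) of cases. It reaches z > 1.96 in only 32% to 4%. A direct female-male difference test at 0.05 detects the difference in 94% to more than 99%. Selecting loci on the primary result does not distort that test at equal weights and equal sampling variances, because the sum and the difference of the two estimates are then uncorrelated.

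**The case against.** **Purpose.** The article does not say that sex differences will be judged. It speaks of similarity, in a secondary item within an open-ended list, and no aim or hypothesis concerns sex. This stands: the analysis can be read as a check that pooled findings hold within each sex, and its weight should be judged accordingly. Such a check still needs a comparator that can fail clearly.

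**Information retained.** A reader might infer that the comparison would show similarity whatever the truth, or that real differences are bound to be reported as consistency. The documents do not support that. They state no metric, threshold or decision rule. At equal weights √((1+r)/2) rises steadily with r, so a value of 0.71 is well short of 1. With unequal weights the smaller sex exposes the difference (0.32 at 75:25), and both sexes are to be analysed. At female-only loci, agreement in sign can mislead, but the male result would usually show no association. These points rule out calling the comparison uninformative. They do not remove the bias, which can be undone only by someone who knows the weights and applies the formula.

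**Detail elsewhere.** The article refers to predetermined analysis plans, and a direct between-sex test may be in one of them. The absence of such a test here is therefore not the point. The point is that the article does state a comparator, and that comparator overlaps with each sex-specific sample.

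**Sex mix.** The Background sentence on equal proportions describes the disorder, not the cases and controls to be analysed. That is right; the 50:50 weight is an assumption.

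**Conclusion.** The point holds in a limited form. Comparing each sex with a primary GWAS that contains it compresses the scale and shifts it towards similarity. With equal weights and equal effect variances, complete absence of shared effects appears as 0.71 and a true correlation of 0.75 as 0.94. With a 75:25 split and no shared effects, the two sexes show 0.95 and 0.32. The exact values depend on the assumed weights and variances. The part-whole dependence does not rest on any one of them, only on the primary GWAS pooling both sexes.

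This affects how a secondary analysis is interpreted. It does not alter the primary GWAS, the aims or the sample size. It is worth correcting because a direct comparison is available from the same sex-specific results.

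**What to change.** Reword the item so that the stated comparison is females against males:
- the LDSC genetic correlation between the female-only and male-only GWAS, reported with its confidence interval and tested against 1;
- at each locus from the primary GWAS, a test of heterogeneity between the female and male effect estimates, or a SNP-by-sex interaction test, corrected for the number of loci.

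Keep the comparison with the primary GWAS as descriptive only. Base any statement that the sexes are similar on the interval for the between-sex correlation.

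The cost is one sentence in the plan and a few further runs on sex-specific summary statistics that are already planned. The drawback is precision: each stratum holds only part of the cases, so the between-sex correlation will have a wide interval and the result may be inconclusive. If a direct test is already in the separate genotype analysis plan, the article's sentence need only be brought into line with it.
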